#### Control group

At baseline, the control group receives a flyer with general recommendations on a healthy diet, based on the Portuguese brief guidance for healthy eating in primary health care [27]. No food baskets or any of the nutritional education strategies are implemented. To promote study adherence, a shopping voucher is given to each participant at the end of the trial. This comparator was chosen to reflect the standard care that could be given by clinicians.

### Data collection

#### Sociodemographic and lifestyle data

The participants' relevant clinical history is collected from their electronic hospital records (disease duration, current medication, and comorbidities). A structured questionnaire was developed to collect patients' age, sex, educational level, menopausal status, smoking status, and family history of rheumatic diseases.

#### Nutritional assessment

Nutritional assessment encompasses four components: nutritional intake, dietary pattern characterisation, body composition analysis, and anthropometric measurements. Nutritional intake is assessed by a 24-h dietary recall (24 h Recall), one of the most widely used tools in nutrition surveys to obtain detailed information about all food and beverages consumed in the past 24 h. A quantitative assessment with portion size quantification is included to provide a more comprehensive and detailed report. Adherence to the MedDiet is assessed with the Portuguese version [28] of the 14-Item Mediterranean Diet Assessment Tool developed by PREDIMED study authors [29, 30], in which a maximum score of 14 points can be achieved, being a strong adherence defined by a score ≥ 10 points. Anthropometric measurements (height, weight, and waist circumference) are performed by registered dietitians. BMI is calculated as weight/height squared (kg/m^2^) and bioelectrical impedance analysis (BIA) is performed to analyse body composition (Fat Mass, Fat-Free Mass, Total Body Water and Body Cell Mass). Nutritional assessment is performed at baseline and at the end of the trial for both groups and every month (baseline, 4th, 8th and 12th weeks) for the intervention group.

#### Clinical outcome measures

The DAS28-ESR and articular ultrasound examination of 28 joints are performed to assess disease activity. The DAS28 is the most widely used scoring system to determine disease activity in patients with RA [31, 32] considering the following items: number of tender and swollen joints in 28 joints (shoulders, elbows, wrists, metacarpophalangeal joints, hand proximal interphalangeal joints and knees); ESR (mm/hr), and a patient global health assessment based on a visual analogue scale (VAS-GH, range, 0–100). The DAS28-CRP is also being assessed as a secondary outcome measure. It encompasses the same items as the DAS28-ESR but substitutes the ESR with CRP in the formula.

Articular ultrasound examination is performed using a GE Logiq E9 equipment with a 6–15 MHz matrix linear probe. Doppler ultrasound (DUS) is used to assess the vascularisation of the synovial tissue. Ultrasound procedures and grey scale ultrasound (GSUS) and DUS grading are based on EULAR-OMERACT consensus [33–35]. The Doppler parameters are adjusted at the maximum sensitivity for slow flow (pulse repetition frequency of 0.4 kHz, lowest wall filter on 45 Hz, and 7.5 MHz Doppler frequency) with Doppler gain just below the noise level. In all patients, the wrists, metacarpophalangeal joints, and proximal interphalangeal joints are examined with ultrasound. Examinations are performed using a standardised dorsal and dorso-lateral scans. Erosions are also evaluated by GSUS as defined by the OMERACT consensus [36] and a semiquantitative score is used to evaluate ultrasound detected erosions [37].

As for patient-reported outcomes, functional status and quality of life are evaluated using the HAQ [38] and SF-36 short form [39] questionnaires, respectively. The HAQ assesses functional status through a disability index, and patient global and pain visual analogue scales [38]. The SF-36 includes a multi-item scale that assesses various health concepts such as limitations in physical activities related to health problems, limitations in social activities related to physical/emotional problems, limitations in day-to-day activities due to physical health problems, pain, mental health, limitations in the day-to-day activities because of emotional problems, vitality, and general health perceptions [39]. Clinical assessments are performed at baseline and after 12 weeks in both groups.

#### Oral and Intestinal Microbiota

Saliva samples are collected with a saliva collection kit while the faeces are self-collected by the participants with the OMNIgene GUT kit. Samples are processed according to the standard operating procedure, which defines biological samples' handling, processing, and freezing protocols to be preserved at the Biobank-GIMM, CAML.

For cell lysis, three bead beating cycles, in a total of 3 min of bead beating are included. We use the Ruptor Elite (OMNI International) with the following conditions: 1 min on at 6 m/s followed by 5 min rest. The bacterial DNA is extracted with the QIAamp PowerFecal Pro DNA Kit (Qiagen). Shotgun metagenomics sequencing will be performed, generating > 3 million reads per sample. The sequencing data resulting from the feces samples will be processed using the bioinformatics pipeline from the Microbiome in Health and Disease Translational Laboratory (GIMM), which includes quality filtering to remove low-quality reads and sequencing artefacts, removal of host DNA reads by mapping to the human genome (GRCh38), and elimination of optical duplicates. To perform taxonomic classification, a combination of k-mer and mapping approaches to a custom-developed reference database will be used, which includes a curated collection of bacterial and fungal genomes from publicly available databases (GTDB, UHGG). Similarly, for functional classification, a combination of k-mer and mapping approaches to publicly available functional databases such as Uniprot, KEGG, CAZy, and others will be used.

#### Lipid profile, inflammation and intestinal permeability biomarkers

Blood tests are performed to determine the serum levels of the lipid profile biomarkers (Triglycerides, Total Cholesterol, HDL and LDL Cholesterol) by standard operating procedures, as well as the serum levels of inflammatory and disease activity biomarkers (CRP and ESR). Although this study protocol encompasses the DAS28-ESR as a primary outcome, the serum CRP levels are also evaluated due to its high sensitivity for evaluating short-term inflammation [40]. Faecal calprotectin, an established marker of gut inflammation, is being analysed by a particle-enhanced turbidimetric immunoassay (CALiaGold© test).

Serum IFABP, lipopolysaccharide-binding protein (LBP) and sCD14 will be evaluated by Enzyme-Linked Immunosorbent Assay (ELISA), once data collection is completed. IFABP actively participates in dietary lipid metabolism by mediating fat absorption through binding and intracellular trafficking of free long-chain fatty acids [41]. Increased serum levels of IFABP, which is also a specific biomarker of gut epithelial integrity, have been shown in RA patients [42]. LBP, an acute-phase protein that carries the ability to bind to LPS [43], has been recognised as a sensitive serum biomarker for RA disease activity, as it significantly correlated with ESR, CRP, tender joint counts, swollen joint counts and DAS28 [44]. CD14s is also an acute phase protein whose hepatic production is increased in response to interleukin (IL)−6 in the setting of inflammation. CD14 stimulates the production of other pro-inflammatory cytokines, including IL-6, in an amplification loop that participates in RA pathogenesis [45]. Furthermore, CD14s has been shown to be increased in RA patients and correlate with DAS28 score and response to treatment [46]. These biomarkers, IFABP (serum diluted 1:4), LBP (serum diluted 1:500), and CD14s (serum diluted 1:15), will be measured from patient serum by sandwich ELISA (LBP cat. DY870; FABP2 cat. DY3078; CD14 cat. DY883; R&D Systems, USA), following the manufacturer instructions. Horseradish peroxidase conjugate will be detected with enhanced chemiluminescence substrate (cat. 32,106, Pierce, USA) and measured with a microplate reader (BMG Pherastar FS, BMG LABTECH, Germany).

Zonulin, a strong modulator of intestinal intercellular tight junctions, is recognised to play a role in the translocation of macromolecules and, consequently, in the tolerance/immune response balance [47]. Higher serum zonulin levels were shown to be accompanied by increased intestinal permeability and, in turn, the disruption of the intestinal barrier function has been proven to occur before the onset of the inflammatory phase of murine and human arthritis [48]. Zonulin (serum diluted 1:10) will be measured from patient serum by sandwich enzyme-linked immunosorbent assay (ELISA) (cat. E-EL-H5560, Elabscience, USA), according to the manufacturer instructions. Optical density will be measured with the microplate reader (BMG Pherastar FS, BMG LABTECH, Germany) set to read the absorbance at 450 nm with a wavelength correction set at 540 nm.

All ELISA assays will be performed in High-Throughput Screening (HTS) mode with reagent and liquid dispensing by the dispenser (CERTUS FLEX Fritz Gyger AG, Germany), serum sample dispensing by dispenser (ECHO 650, Labcyte, US) or manually, and washes by plater washer (EL406, Agilent BioTek, USA). These assays will be performed at the Finnish Institute for Molecular Medicine Finland (FIMM) High Throughput Biomedicine unit.

#### Intestinal permeability: lactulose/mannitol test

Intestinal Permeability is assessed through the lactulose/mannitol (Lac/Man) test, a gold standard for functional measurement of intestinal permeability in humans. Specific dietary recommendations for the 24 h before the test are provided to standardise conditions across participants and reduce variability in results. Although there is no consensus for dietary restrictions in this test, patients are advised to avoid some foods and beverages potentially containing lactulose and/or mannitol [49–51], such as dairy products, sweet potato, mushrooms, cauliflower, butternut squash, celery, peas, green beans, chicory, fennel, kimchi, sauerkraut, peach, watermelon, gelatin, gummies, candies, chewing gum, sauces, ‘diet’ and ‘light’ food products, artificial sweeteners, dietary supplements, soft drinks, and flavoured and alcoholic beverages.

After an overnight fast (≥ 8 h), patients are given a solution containing 5 g of lactulose and 1 g of mannitol and are encouraged to drink 1.5 L of water for 4 h and collect all the urine produced during that time. Lactulose and mannitol concentrations are determined by ultra-performance liquid chromatography-tandem mass spectrometry (UPLC-MS/MS). The lactulose and mannitol quantification is performed at Instituto Nacional de Saúde [name] in Lisbon, Portugal. UPLC-MS/MS and mass spectrometer conditions are further detailed in the supplementary material.

#### Endotoxemia: LPS biological activity

Toll-like receptor 4 (TLR 4) activation reflecting LPS bioactivity will be measured, when recruitment has finished and all samples have been collected, with HEK-Blue hTLR4 reporter cells (InvivoGen) engineered to produce secreted alkaline phosphatase in response to TLR4 stimulation. The method has been established and validated for cell-based High Throughput Screening, making it appropriate for population cohort sample screening [52]. Briefly, 70,000 cells/well will be seeded on a 384-well plate with 25 μl of cell culture media. Serum samples (2.5ul) will be added in duplicates to wells to obtain a final working concentration of 1% (v/v) per well. To determine whether TLR4 activation is due to LPS, we will add another set of sample duplicates with 0.1 mg/ml of polymyxin B (InvivoGen), an LPS inhibitor. Human AB serum 1% (v/v, Sigma-Aldrich) will serve as a negative control. A set of standard dilutions will be created with LPS-B5 Ultrapure from *Eschericia coli* O55:B5 (InvivoGen) diluted in endotoxin-free water with 1% Human AB serum. After incubation at 37° C for 24 h, we will add 10ul/well SEAP substrate QUANTI-BlueTM Solution (InvivoGen). Following a 6 h incubation at 37 °C, absorbance will be measured with a microplate reader (BMG Pherastar FS, BMG LABTECH, Germany). TLR4 activation due to LPS will be then determined by subtracting the activity remaining in the presence of polymyxin B from the total TLR4 activation measured. A linear standard curve will be plotted. The LPS biological activity will be performed at the Helsinki University (Finland).

#### Proteomics

Nowadays, various proteomic techniques are being applied to different biological samples, from both RA patients and experimental animal models, showing promise in identifying novel biomarkers and treatment targets [53]. In our trial, once all samples have been collected, blood serum samples will be studied through micro-liquid chromatography-mass spectrometry (micro-LC–MS/MS) using a hybrid quadrupole TripleTOF 6600 (Sciex, CA, USA). The proteomes will be identified through the qualitative shotgun data-dependent acquisition (DDA) method [54, 55], and protein levels will be measured through the quantitative sequential window acquisition of all theoretical mass spectra (SWATH) methods. A 5% false discovery rate (FDR) and a p-value ≤ 0.05 will be used to filter the dataset. FunRich software 3.1.3 will be used to determine proteome enrichment.

#### Serum Glycome characterisation

When patient recruitment has been concluded, serum will be processed and ultra high performance liquid chromatography (UHPLC) analysis will be performed using hydrophilic interaction liquid chromatography (HILIC) chromatography coupled with fluorescence detection and online electrospray MS for total serum glycome characterisation. From this analysis we will be able to identify unique signatures related with plasma proteins N-glycans alterations that can be associated with dietary intervention. Then, and given the fact that Fc glycosylation of IgG/IgA is a key factor for the definition of effector (inflammatory) function of IgG/IgA, we will characterise the antibody specific Fc glycosylation of IgG/IgA at the different time points before and after dietary intervention, by advanced glycoproteomics nano-liquid chromatography-electrospray ionization-tandem mass spectrometry (nanoLC-ESI–MS). The structural characterisation of the IgG Fc-N-glycans in terms of composition and abundance will be performed by advanced liquid chromatography coupled to mass spectrometry), that enables high-throughput analysis of IgG Fc-glycans in a subclass-specific manner.

Figure 2 resumes all variables collected during the study timeframe.

**Fig. 2 Fig2:**
[figure not shown]
– Overview of the data collection throughout the trial. Visual representation of the specific variables to be collected in each phase of the study, which are identical at baseline and at the end of the trial (12th week) for both groups. Only the intervention group (MedDiet +) has in-person follow-up consultations with nutritional assessment at 4th and 8th weeks. *Sociodemographic and lifestyle data are also collected at baseline. Abbreviations: CRP: C-reactive protein; DAS28: Disease Activity Score using 28 joint counts; ESR: Erythrocyte sedimentation rate; HAQ: Health Assessment Questionnaire; I-FABP: Intestinal-fatty acid binding protein; LPS: Lipopolysaccharides; PREDIMED: Prevención con Dieta Mediterránea; SF36: 36-Item Short Form Health Survey

#### Data management and statistical analysis

Collected data files in paper format are being securely stored in locked filing cabinets within the Nutrition Lab, FMUL, CAML, accessible only to authorized team members. All recorded data and collected samples are coded, and analysis will be performed anonymously. Only members of the research team will have access to data and samples. FMUL has the property of the resulting data and the right to disclose the results as merged data analysis. The Nutrition Lab of FMUL will have access to the final trial dataset and will be responsible for storing conserved data for five years after the last publication.

Statistical analysis will be conducted using SPSS (SPSS® Inc., Chicago, IL) version 28.0 or a subsequent updated version. The Normal data distribution will be verified using the Kolmogorov–Smirnov tests, considering the sample size. Depending on the normality of the data, parametric or non-parametric tests will be used. A *p*-value of less than 0.05 will be considered statistically significant. Descriptive statistics will be used to describe all variables, both by groups (intervention vs. control) and by timing (baseline and final visits). Characteristics between groups at baseline will be compared to identify significant differences that may confound results. To access differences between the baseline and the end of the intervention (paired sample test) as well as between groups (independent samples test), the student's T-Test or its non-parametric equivalent will be used. Multiple regression analysis will be conducted to address the influence of baseline characteristics. An analysis of covariance (ANCOVA) will be carried out when baseline differences need to be controlled, being the group (intervention/control) the independent variable, and the covariates the baseline characteristics and demographic data. To test how the MedDiet + pattern influences the study endpoints, a multivariate analysis of covariance (MANCOVA) will be conducted to assess group differences with multiple dependent variables and adjusting for confounding factors. The existence of a control group allows for statistical comparisons between groups and ensures the true effectiveness of the MedDiet + when adjusting for potential confounders.

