#### Primary endpoint

Change of DAS28-ESR (Disease Activity Score in 28 joints calculated with erythrocyte sedimentation rate) from baseline to 12 Weeks.

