### Recruitment and eligibility criteria

RA patients diagnosed according to the ACR/EULAR2010 criteria [23], aged 18 years old or older, are invited to participate in this study if eligibility criteria are met at their regular follow-up RA consultations. All participants sign a written informed consent form before any study procedures. Our inclusion criteria are diagnosis duration of at least one year, active disease (DAS28-ESR ≥ 2.6 units), stable medication for at least 12 weeks prior to the baseline assessment (including intra-articular steroid injections), and a low or medium adherence to the MedDiet (defined as a score of < 10 points in the 14-item tool by the PREvención com DIeta MEDiterránea trial, PREDIMED). Patients requiring therapeutic adjustments and/or intra-articular steroid injections during the trial are excluded. Our exclusion criteria are: antibiotic therapy within 4 weeks before enrolment; prednisolone dose > 7.5 mg/day; persistent use of non-steroidal anti-inflammatory drugs: diagnosis of inflammatory or irritable bowel disease, celiac disease, chronic diarrhoea; diagnosis of other immune-mediated or inflammatory diseases; major organ dysfunction; cancer diagnosed in the last five years; presence of health conditions which may impair the ability to consent to study participation (cognitive impairment/psychiatric disease). Regarding the use of antibiotics, although a general recommendation for a washout period is challenging to define, according to literature, a minimum of 4 weeks since cessation of antibiotics is recommended [24] and is considered in this trial. The overall diagram flow of the study is shown in the SPIRIT figure illustrated in Fig. 1. The SPIRIT checklist is provided as supplementary material.

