Another strength of the TASTY study design is that the dietary intervention goes beyond merely providing a dietary plan, addressing a key limitation in previous dietary trials: participants' difficulty in adhering to recommendations. Several nutritional education strategies are implemented based on the "Clinical Culinary" concept to ease the process of changing eating habits and maximise the effects of the nutritional intervention. Clinical Culinary is a new, evidence-based component of clinical care that incorporates knowledge of nutrition science, including food and cooking, into current medical disease prevention and treatment [76]. The main goal of this approach is to create a positive behavioural change by equipping patients with the knowledge and practical skills needed to improve their health. The systematic delivery of food baskets will also help ensure standardised access to the recommended foods, which is crucial to make sure participants from different financial backgrounds have the means to successfully implement the nutritional intervention. Additionally, the content of the food baskets provided to participants will carefully be selected by the registered dietitians according to the MedDiet principles, meaning that minimally processed foods will be chosen. For instance, plain yoghurt will be provided to minimise participants' consumption of food additives, such as artificial sweeteners, due to their reported effects on gut microbiota [77]. This trial will also allow us to address if significant differences in dietary intake and clinical outcomes may be achieved by standard care that could be given by clinicians (control group) and to which degree a structured nutritional plan developed by registered dietitians (MedDiet +) implies additional benefits. Weaknesses of this trial include the inability to observe long-term effects beyond the intervention period and the reliance on self-reported food intake, which is susceptible to inaccuracies. However, the close follow-up during the intervention period, along with the educational and patient empowerment strategies, were designed to mitigate these limitations. Regarding eligibility criteria, the exclusion of antibiotics for only four weeks before baseline may represent an additional limitation, as different treatment schemes can impact gut microbiota in distinct ways. The class of antibiotics, the dosage, the route of administration, and the characteristics of the individual are some of the reported mechanisms that justify the varying disturbance caused by antibiotics in the microbial communities of the gut [78].

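### Before-after tests and the claim about what standard care achieves: the design supports only the comparison between the randomised arms

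*Protocol article*

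**What the plan says.** All references are to the protocol article.

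- **Data management and statistical analysis.** Two comparisons share one sentence: "To access differences between the baseline and the end of the intervention (paired sample test) as well as between groups (independent samples test"). One general rule covers both: a p "value of less than 0.05 will be considered statistically significant". Descriptive statistics by group and by visit are listed separately, so the paired test is an inferential one. The same section plans ANCOVA and MANCOVA between groups.
- **Discussion.** The trial is said to "address if significant differences in dietary intake and clinical outcomes may be achieved by standard care that could be given by clinicians (control group"). The sentence then raises, as a second question, what MedDiet + adds.
- **Control group.** The comparator is a flyer with general healthy-eating advice, given once at baseline. The only other arm receives the full programme.
- **Recruitment and eligibility criteria.** Entry requires "active disease (DAS28-ESR ≥ 2.6 units") and a PREDIMED adherence score below 10. Patients are invited "if eligibility criteria are met at their regular follow-up RA consultations".
- **Primary endpoint.** Change in the same score, DAS28-ESR, "from baseline to 12 Weeks".
- **Clinical outcome measures.** "Clinical assessments are performed at baseline and after 12 weeks in both groups". The text does not say whether the reading that qualified the patient is also the baseline reading.

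**The concern.** The first Discussion question differs from the between-arm comparison, which the same sentence raises separately. With no arm free of dietary advice, it can be answered only from the control arm's change over 12 weeks. That change has several sources besides the leaflet:

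- the natural course of the disease;
- unblinded participants, whose global health rating is part of DAS28;
- exclusion of patients who need a treatment adjustment during the trial, which tends to remove those who worsen;
- regression to the mean, if the value that had to exceed 2.6 is also the starting value. Dietary adherence, selected by a PREDIMED ceiling, is open to the same problem in the other direction.

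Two wrong conclusions become available. A significant fall in the control arm could be credited to standard care. A significant fall in MedDiet + alone could be read as a treatment effect, although a difference in significance is not a test of the difference between arms.

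**Working it through.** The plan gives no figure to reproduce: the 100 participants are a convenience sample, with no mean, SD or correlation for DAS28-ESR.

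**Inputs from the article.** Entry cut-off 2.6; 50 patients per arm; p < 0.05 (taken as two-sided); readings at baseline and week 12.

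**Assumptions, not from the article.** Clinic mean μ 3.0 to 3.5, SD σ 1.2 to 1.3, correlation ρ between the two readings 0.5 to 0.9, bivariate normal values, no effect in either arm, and the qualifying reading used as baseline.

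**Formulas.** With a = (2.6 − μ)/σ and λ = φ(a)/(1 − Φ(a)):

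- expected fall = (1 − ρ) × σ × λ
- SD of change = √[(1 − ρ)²σ²(1 + aλ − λ²) + σ²(1 − ρ²)]

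**Largest effect in the range** (μ 3.0, σ 1.3, ρ 0.5)
- a = −0.308, λ = 0.613
- fall = 0.5 × 1.3 × 0.613 = 0.40
- SD of change 1.205; standard error 1.205/√50 = 0.170; ratio 0.398/0.170 = 2.34
- simulated paired-test rejection: 63%

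**Smallest effect in the range** (μ 3.5, σ 1.2, ρ 0.9)
- a = −0.750, λ = 0.389
- fall = 0.1 × 1.2 × 0.389 = 0.05
- SD of change 0.531; standard error 0.075; ratio 0.047/0.075 = 0.62
- simulated rejection: 9.7%, or 9.2% counting falls only

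**Central illustration** (μ 3.2, σ 1.2, ρ 0.75)
- fall = 0.25 × 1.2 × 0.509 = 0.15
- the paired test rejects in 25% of arms, and in at least one arm in 44% of trials
- without selection, the same simulation gives 4.8% per arm and 9.7% for at least one arm

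**MedDiet + significant, control not.** With independent arms and rejection probability p in each, this is p(1 − p). At p = 0.097 it is 0.097 × 0.903 = 0.09. It peaks at 0.25 when p = 0.5, which lies inside the range. So it occurs in about 9% to 25% of trials (19% in the central case).

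**Fresh baseline after a separate qualifying visit.** The fall becomes (r₁ − r₂) × σ × λ, where r₁ and r₂ are the correlations of the qualifying reading with baseline and with week 12.
- Equal correlations: fall 0, simulated rejection 4.9%.
- r₁ = 0.85 and r₂ = 0.75, central μ and σ: 0.10 × 1.2 × 0.509 = 0.06.

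**Between-arm test on change.** Simulated type I error is 5.2% in the central case and about 5% throughout, because the selection acts equally on both randomised arms.

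**The case against.** The strongest reply is that the article already ties effectiveness to the control group: MANCOVA is to assess group differences, and the existence of a control group is given as what permits the comparison. Nowhere does it say that efficacy will be inferred from significance in one arm and not the other. That stands. A reader might infer that the paired tests are meant as the evidence for MedDiet +, but the text does not say so. Even that the paired tests are run separately in each arm is an inference, though a natural one given the Discussion sentence.

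Secondly, a reader might conclude that selection at 2.6 necessarily makes both arms fall. The article does not support this. Eligibility is judged at routine consultations, and the baseline assessment may be a new reading, in which case the fall could vanish. Stable medication before entry also makes a high correlation, and so a small fall, plausible.

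Thirdly, one could count every trial in which exactly one arm is significant, whichever arm it is. That doubles the figure and overstates the harm, since only one direction favours MedDiet +.

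None of this rescues the Discussion claim. It fails even with no regression to the mean, because a before-after change without a suitable comparator cannot isolate the leaflet.

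**Conclusion.** The point holds, within limits. The article announces a conclusion about standard care that its design cannot deliver, and it gives before-after tests the same inferential standing as the randomised comparison. This part needs no assumed numbers.

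The size of the regression component is conditional. If the qualifying DAS28-ESR is the baseline value, and under the assumed means, SDs and correlations, the expected fall without any effect is about 0.05 to 0.40 units. A paired test shows a significant fall in about 9% to 63% of arms. Under a separate baseline reading it may be close to zero.

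It would be wrong to infer that the primary comparison is compromised: the randomised between-group test is not biased by this selection. The defect is confined to before-after inference and to the Discussion statement.

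**What to change.** 1. In the statistical section, make within-arm change descriptive: mean change with 95% confidence interval and no significance claim.
2. State that every claim of effect rests on the between-group difference adjusted for the baseline value.
3. In the Discussion, delete the claim about what standard care achieves. Keep only the question of what MedDiet + adds over the leaflet.
4. State whether the DAS28-ESR that qualifies a patient is also the baseline value.

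Baseline adjustment of EULAR response and of DAS28-ESR < 2.6 may improve precision but is optional. It does not follow from this problem, because regression to the mean affects both arms alike.

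The cost is wording and analysis labelling only; no additional data are needed.
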